### Setting

DAILY is a single site study conducted at the specialist ward for addiction disorders and the outpatient clinic for substance use disorder of the Clinic for Psychiatry and Psychotherapy at the University Hospital of Munich. There are 24 patients with a minimum age of 18 years on the ward, with men and women admitted equally. The day clinic treats 15 patients with a minimum age of 18 years simultaneously. On the ward and in the day clinic there are fixed, individually determined schedules for therapy sessions from which patients are not allowed to deviate. Meals are offered by the clinic at fixed times of the day, but do not have to be taken. Patients are free to leave the ward and the day clinic between therapy sessions in order to take meals outside or to pursue other activities such as walks or sports. The ward is open in principle, but care is taken to ensure that patients do not leave it between 10 pm and 8 am. There are no fixed sleeping hours on the ward, except that patients must arrive on time for their therapy sessions, which usually start between 08:30 and 11:00 am. On the weekend, patients of the ward have no regular appointments. Patients of the Day Clinic leave the clinic in the afternoon and arrange the rest of the day and their weekends independently. In addition, food can be brought to the ward and the day clinic and snacks can be eaten at any time. Both clinics are interdisciplinary staffed by medical doctors, psychologists, nurses, and social workers, all of whom have broad experience in the treatment of substance use disorders, including AUD. About half of the patients on both sites are diagnosed with AUD, the other half suffers from multidrug dependency. On the ward a qualitative detoxification program with psychotherapeutic services is offered to AUD patients and patients with multidrug use. In the day clinic the same psychotherapeutic services are offered as on the ward, but the patients are already detoxified, and the therapy takes place on a day-care basis.

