### Standard Therapeutic Services on the Ward and the Day Clinic

In parallel to the DAILY or the sham treatment, all patients receive the standard clinical treatment consisting of medical and psychological consultation, individual and group therapy (combining Motivational Enhancement Therapy and Cognitive Behavioral Therapy), and medication if necessary. The psychotherapeutic treatment of AUD and multiple substance use patients is the same but is conducted separately. The standard psychotherapy concept of the ward and the day clinic includes motivation work in which the incentive to abstinence and the decision to change consumption behavior is increased. In addition, situation analyses, the identification of risk factors, and the development of alternative actions are used to work with patients on relapse prevention. In addition, all patients receive psychoeducational therapy sessions to provide theoretical knowledge about the definition of addiction and its development on a neurobiological level. The treatment of AUD patients on the ward is scheduled for 14 days. In the day clinic, the treatment time ranges from 2 to 4 weeks and the concepts described above are elaborated in more detail and sociotherapy is also offered. In none of these standard therapies the advantages of daytime structures and regular sleep times are discussed.

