### Study Population

Men and women, unemployed and employed subjects are equally included in the study. Depending on whether the subjects are patients of the ward or day clinic, they are in detoxification or post-detoxification treatment. Study enrollment of subjects who are newly admitted to the detoxification program of the ward will take place at the earliest after 5 days of detoxification, to exclude cognitive and physical limitations caused by acute intoxication and its after-effects. Study participants who are discharged from the ward either go home, receive further treatment in the day clinic, or go to other institutions for long-term therapy. Study participants who are discharged from the day clinic either go home after discharge or go to other institutions for further treatment. The health conditions of all test persons allow them to perform their daily tasks without external assistance. Approximately half of the study subjects have a regular job, while the others are unemployed or retired. Usually 3–5 subjects are involved in the study simultaneously.

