### Recruitment

In order to facilitate recruitment, a logo was designed for the DAILY study, which has a high recognition value for the test persons and underlines the official character of the study (Figure 2). After screening for eligibility, participants are recruited during their clinical stay at either the specialist ward or the outpatient clinic for addiction disorders. A member of the study staff addresses the candidates personally and finds out whether there is in principle interest in participating in a concomitant therapy study for AUD patients. Candidates are given at least 1 day to consider. In the event of positive feedback, they are allocated to either the intervention or control group.

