### Informed Consent and Baseline Assessments

To participate in the study, all participants need to sign an informed consent in the 1st week (Figure 1). Afterwards, irrespective of the group allocation, a semi-structured interview is conducted to assess demographical data: age, gender, employment status, occupation, and marital status. Medical data are evaluated as well: size, bodyweight, blood pressure, current medications, and information about previous alcohol problems and possible depressive episodes. In addition, the questionnaires described below (Table 1) are filled out together with the participants. Lastly, blood samples are collected. This appointment is also used to prepare the test persons for the topics and contents of their respective groups.

**Table 1 T1:** Overview of questionnaires, physiological assessments, and time points.

**Assessment category**	**Assessment instruments**	**First session**	**Last session**	**Between sessions**
Baseline	Demographics	x		
Circadian	Sleep-Food-Diary			x
	Munich ChronoType Questionnaire (MCTQ)	x	x	
	Pittsburgh Sleep Quality Index (PSQI)	x	x	
Alcohol use	Alcohol use disorders identification test (AUDIT)	x	x	
	European Addiction Severity Index (EuropASI)	x	x	
	Timeline Followback 30 (TLFB)	x	x	
Depression	Hamilton Depression Scale (HAMD)	x	x	
	Inventory of Depressive Symptomatology (IDS-SR)	x	x	
Self-efficacy	Self-Efficacy Questionnaire (SWE)	x	x	
Blood values	Blood draws	x	x	

The further course of the study and the contents of the following appointments are described separately for the intervention group and the control group.

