Additionally, a questionnaire specially designed for this study with a total of 30 questions and a 4-step ordinal scale for the answers to assess the rating of the participants' subjective structuredness in their everyday life will be filled out. This questionnaire includes, for example, questions on the subjective assessment of whether activities such as eating, sleeping and sport are carried out regularly, whether relapses are associated with irregular daily routines, and whether the craving for alcohol usually occurs at the same time of day. To give the subjects of the control group no indication of the actual aim of the study, the questions that aim at the circadian daily structure are mixed with neutral questions.

Drinking behavior and daily craving will be assessed with questionnaires and the diary, respectively (Table 1). General drinking habits of the last few weeks are surveyed using the AUDIT questionnaire. In addition, the European Addiction Severity Index (EuropASI) is used, which covers not only alcohol and drug consumption but also physical, psychological, financial, and social problem areas of addicted patients. The number of alcoholic drinks and the number of alcohol-free days within the past 30 days is assessed by means of the Timeline Followback 30 (TLFB-30). The diary, which the subjects fill out to collect the Routine Variability Scores, additionally records the highest craving for alcohol on a scale of 0–10 of each day.

According to our secondary hypothesis that the stabilization of circadian rhythms contributes to the reduction of depressive symptoms and increased well-being, changes in the affective state, with a focus on depressive symptoms, are measured with the external assessment questionnaire Hamilton Depression Scale (HAMD) and with the self-reporting questionnaire Inventory of Depressive Symptomatology (IDS-SR). Sleep quantity and quality will be assessed by Pittsburgh Sleep Quality Index (PSQI). Furthermore, for measuring if the DAILY structure program will influence the feeling of self-efficacy, we will employ the Generalized Self-Efficacy Scale (GSES).

As exploratory outcomes, it will be documented how many subjects in the DAILY intervention group and the control groups discontinue the therapy. Furthermore, possible changes of the chronotypes in the course of the study will be defined by the Munich ChronoType Questionnaire (MCTQ).

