## Data Analysis

All statistical analyses will be performed using SPSS software version 25 (SPSS INC., Chicago, IL, USA). Sociodemographic data, chronotype, diary data and blood parameters will be reported in form of descriptive statistics. Continuous variables will be presented as mean ± *SD* and normality of continuous data will be measured by using the Kolmogorov-Smirnov-Test. Accordingly, we will use parametric and non-parametric analyses. For all calculations, the significance level will be determined at α < 0.05.

Data analysis will be performed according to intention-to-treat analysis (ITT) rules. In particular, this means that all subjects who completed the questionnaires of the first session and the 1st week of the diaries are included in the analysis, regardless of whether their subsequent data sets are complete or whether they have dropped out of the study. This is done by imputing missing data with the help of all available data that was assessed until then. Participants who withdraw their consent and were not assessed with baseline measurements will be treated as dropouts. All other subjects regardless from the study condition will be analyzed according to ITT.

The data will be evaluated in three different ways: First, outcomes of the endpoint of the study will be compared between the intervention and control groups using unpaired group analyses (e.g., Student's *t*-test, Mann-Whitney *U*-test, Kruskal-Wallis test, one-way ANOVA). Secondly, within-subject analyses of the intervention and control groups are performed, comparing the changes between the start and end of the study of the two groups (e.g., two-way ANOVA). Thirdly, the data are calculated independently of group membership in two-dimensional linear regression using the Routine Variability Scores as an independent variant.

Additionally, statistical differences in the frequency of dropouts between the two groups are calculated using chi-square tests and survival analyses. Multiple regression analyses will be applied to investigate the degree to which predictor variables (i.e., Routine Variability Scores, depression level, severity of alcohol consumption behavior, and self-efficacy score) contribute to outcomes of primary and secondary measures.

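### The baseline TLFB-30 window mixes pre-admission drinking with a varying number of treatment days, so start-to-end change depends partly on when and where the patient enrolled

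*Protocol article*

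**What the plan says.** Drinking behaviour is one of the first primary outcomes (Measured Outcomes). It is measured with AUDIT, EuropASI and TLFB-30. TLFB-30 is the one described as counting drinks and alcohol-free days: "the number of alcohol-free days within the past 30 days is assessed by means of the Timeline Followback 30 (TLFB-30". Table 1, under Informed Consent and Baseline Assessments, lists "Timeline Followback 30 (TLFB" at the first and last session. Nothing in the article moves the first window back to before admission.

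The first session does not come at a fixed distance from the last drinking period:

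- Ward patients (Study Population): enrolment "will take place at the earliest after 5 days of detoxification".
- Ward stay (Standard Therapeutic Services on the Ward and the Day Clinic): "The treatment of AUD patients on the ward is scheduled for 14 days".
- Day-clinic patients (Setting): "the patients are already detoxified, and the therapy takes place on a day-care basis".
- Day-clinic stay (same section as the ward stay): "In the day clinic, the treatment time ranges from 2 to 4 weeks".
- Recruitment: "Candidates are given at least 1 day to consider". This day may run inside the first 5.

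Data Analysis lists an unpaired endpoint comparison first. Second come within-subject analyses, "comparing the changes between the start and end of the study of the two groups". It also names severity of alcohol consumption behaviour as a regression predictor, without saying which instrument supplies it.

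**The concern.** A baseline drinking measure should describe drinking before treatment. This one describes a blend of pre-admission days and days in care. The proportions are set by setting and enrolment day, not by the patient's drinking. Two patients who drank alike before admission and do equally well by week 6 can then show very different changes, one of them with the opposite sign.

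Three uses are affected. Within-arm change in TLFB cannot be read as response to treatment. Comparisons of change between arms carry variance from enrolment timing and are open to chance imbalance in the ward/day-clinic mix. If the severity predictor is taken from the baseline TLFB, it partly measures time since admission. The Design section describes the trial as a pilot to guide a later main trial, so TLFB change estimates and SDs taken from it would carry the artefact forward.

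**Working it through.** The article gives no figure to reproduce. The steps below use its stay lengths plus assumptions that are marked as such.

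**1. Treatment days in the baseline window.** Let d be the days in care before the first session. Treatment days in the window = min(d, 30).

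- Ward, earliest: d = 5, so 5/30 = 17%.
- Ward, end of stay: d = 14, so 14/30 = 47%.
- Day clinic after a full ward stay (inferred): d reaches 14 + 28 = 42, so 30/30 = 100%.

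Only the 5 is stated as an enrolment limit, and only for ward patients. The upper end is derived from stay lengths; no time since detoxification is given for day-clinic patients.

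**2. Change for one patient.** Assume drinking on a share q of pre-admission days and none in care. Baseline alcohol-free days = 30 − q(30 − d). With 24 alcohol-free days at the end in every case, the change is:

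| q | d = 6 | d = 14 | d = 28 | d = 30 or more |
|---|---|---|---|---|
| 50% | +6.0 | +2.0 | −5.0 | −6.0 |
| 80% | +13.2 | +6.8 | −4.4 | −6.0 |
| 100% | +18.0 | +10.0 | −4.0 | −6.0 |

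For example, q = 0.8 and d = 6 gives 30 − 0.8 × 24 = 10.8, and 24 − 10.8 = +13.2. With a window ending before admission, baseline at q = 0.8 is 30 × 0.2 = 6 whatever d is.

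**3. Group level, no treatment effect.** Assume half ward (d even over 6–14, mean 10), half day clinic (d even over 15–30, mean 22.5), q = 0.8, and each end day alcohol-free with probability 0.8 in both arms.

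- Mean change, ward: 24 − (30 − 0.8 × 20) = +10.0.
- Mean change, day clinic: 24 − (30 − 0.8 × 7.5) = 0.0.
- Variance of d: (6.67 + 21.25)/2 + 6.25² = 53.02.
- Variance of change: endpoint 30 × 0.8 × 0.2 = 4.80; timing 0.64 × 53.02 = 33.93; baseline sampling 13.75 × 0.16 = 2.20. The sum is 40.93, SD 6.4, against √4.80 = 2.2 for the endpoint.

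A simulation on these assumptions (20,000 runs, 20 or 40 per arm) gave the same means and SDs. The between-arm difference in change was about 0, with type I error 4.8% to 5.2% (endpoint: 4.8% to 5.3%).

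**4. Chance imbalance.** A 60:40 split in one arm against 40:60 in the other shifts mean change by 0.2 × 10.0 = 2.0 days. With 90% drinking days, ward enrolment on days 5–14 and day-clinic enrolment on days 15–42, mean baseline drinking days are 0.9 × 20.5 = 18.45 and 0.9 × 120/28 = 3.86. The gap is 14.6 and the shift 0.2 × 14.6 = 2.9 days.

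**5. Baseline as a severity measure.** Let q vary between patients with mean m and SD s, independently of d. With the d distribution of step 3, E(30 − d)² = 13.75² + 53.02 = 242.08. Ignoring sampling of days, the correlation between baseline as written and pre-admission drinking is 13.75s / √(242.08s² + 53.02m²). At m = 0.8 this is 0.23, 0.42 and 0.55 for s = 0.1, 0.2 and 0.3.

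**6. Does anchoring always shrink the SD of raw change?** No. Baseline variance is 242.08s² + 53.02m² as written and 900s² anchored. Anchoring reduces it only if s < m√(53.02/657.92) = 0.284m: below 0.26 at m = 0.9, but below 0.14 at m = 0.5.

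**The case against.** The strongest reply is that randomisation deals with this. Enrolment timing is settled before allocation and is independent of it, so the arms have the same expected mix. A reader might infer from the group figures that the trial would find a false DAILY effect. The documents do not support that: step 3 shows no bias and a correct type I error, and the imbalance in step 4 is ordinary chance variation already covered by the standard error.

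The first-listed analysis compares endpoints and does not use baseline TLFB. For dropouts, the imputation rule could bring it in, but the method is not described, so nothing is claimed there.

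It would also go too far to call baseline drinking useless as a predictor. AUDIT, EuropASI, alcohol history and blood markers are collected too, and the severity predictor is not tied to TLFB. Nor are days in care proven abstinent days: ward patients may go out between sessions, and day-clinic patients spend afternoons and weekends away. A statement that every baseline contains 5 to 30 abstinent days would go beyond the text.

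Finally, a pre-admission baseline has its own limits. Recall lengthens, the within-arm change then includes the effect of detoxification, and raw change may not become less variable (step 6). All of these objections stand, and they narrow the point. None of them makes the baseline comparable between patients.

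**Conclusion.** The point holds in a limited form. Followed as written, the plan yields a TLFB baseline with at least 5 treatment days of 30 for ward patients, and possibly 30 of 30 for day-clinic patients. Start-to-end TLFB change is therefore partly an artefact of enrolment timing. Under the assumptions in steps 2 and 3, the same patient's change ranges from +13.2 to −6.0 days at 80% pre-admission drinking, and mean change differs by 10 days between settings without any treatment effect. These sizes rest on assumed drinking rates, no drinking in care and assumed enrolment days; the inclusion of treatment days for ward patients does not.

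The randomised comparison is unbiased in expectation. The harm is limited to within-arm change, noise and chance imbalance by setting in the change analysis, and a weak severity predictor if TLFB supplies it. TLFB-30 is one of three drinking instruments, so this does not undermine the primary outcome as a whole. It is a worthwhile and inexpensive improvement, not a fatal flaw.

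**What to change.** At the first session, take the TLFB for the 30 days ending on the day before admission for the current detoxification; for day-clinic patients, the last day before their own detoxification began. Use it as baseline drinking in both arms. Record admission, transfer and discharge dates so that days in care can be identified in either window.

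Base the between-arm inference on the endpoint TLFB adjusted for this baseline and for ward or day clinic, not on raw change. Adjustment avoids relying on the precision gain that step 6 shows is not guaranteed. According to the Allocation section, the study code already carries the current ward. State that within-arm change includes the effect of detoxification in both arms and is not to be read as an effect of DAILY.

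The cost is one changed instruction, with the same instrument and interview. Recall for day-clinic patients reaches further back: with d = 42, to 42 + 30 = 72 days instead of 30, or up to about six more weeks. Days in care within the endpoint window remain; the recorded dates at least make them visible.

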## Abstract

**Background:** Hallmarks of alcohol use disorder (AUD) are disturbances of circadian rhythms and everyday structures. While circadian rhythms dictate the timing of daily recurring activities such as sleep, activity, and meals, conversely, these activities represent time cues, so called *Zeitgebers*, that the circadian system uses to synchronize with the environment. Here we present a study protocol for our newly developed therapy approach for AUD patients, in which we take advantage of this mutual influence and stabilize and strengthen their circadian system by creating strict daily schedules for daily *Zeitgeber* activities. Since every person has a circadian system with its own characteristics and is subject to social obligations, the daily plans are personalized for each test person. Our hypothesis is that a regular exposure to *Zeitgebers* stabilizes behavioral and physiological circadian rhythms and thereby reduces the risk of alcohol relapses and depressive symptoms and facilitates physical recovery in AUD patients during the 1st weeks of their addiction therapy.

**Methods/design:** The study is a 6-weeks single site trial with a controlled, randomized, single-blinded, parallel-group design including patients with a diagnosis of AUD. The study runs parallel to the standard addiction therapy of the clinic. Patients are randomly assigned to either an intervention group (DAILY) or a sham control group (placebo treatment). Questionnaires and physiological assessments of both groups are conducted before and immediately after the intervention or control treatment. According to our hypothesis, the primary outcomes of this study are improvements of regularity, alcohol consumption, and relapse rate in AUD patients compared to AUD patients receiving control treatment. Secondary outcomes are reduced depressive symptoms and increased physical recovery.

**Discussion:** This study is a randomized controlled trial to investigate the efficacy of a personalized circadian *Zeitgeber* therapy as an adjunctive treatment for alcohol use disorder patients. The overall goal of this and more extended future studies is the development of an adjunctive therapy for AUD patients that is uncomplicated in its use and easy to implement in the clinical and everyday routine.

**Trial registration:** This study is registered at the German Clinical Trial Register with the trial number DRKS00019093 on November 28, 2019.

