### Circadian *Zeitgeber* Therapy for AUD Patients in the Transition From Inpatient to Outpatient Care

For AUD patients, the transition phase between the inpatient stay and discharge from the clinic to outpatient care or home often represents a stressful and thus susceptible time for alcohol relapses and a worsening of the general psychiatric health situation (55). For patients the sudden change from the clinical environment back to autonomous self-organized daily routines is often very difficult (56). During this transition phase, daily rhythms such as sleep-wake cycles and mealtimes become irregular and often drift into a later phase, which has been associated with a worsening of psychiatric symptoms, including alcohol relapses and depression (57, 58).

Within the framework of psychotherapy the suggestion of structuring the everyday life in an orderly manner to psychiatric patients, especially AUD patients is not new (59). This therapy component of self-management has positive psychological effects such as reducing stressful situations and enhancing the feeling of self-efficacy. However, we have designed a study that, in addition to previous therapy programs, has a special focus on the transition time between inpatient and outpatient care or home, and which focuses on the targeted use of strong *Zeitgebers* to restore and stabilize physiological circadian rhythms in AUD patients. Similar circadian reinforcement therapies have been proven for bipolar disorder (60, 61) and are currently tested in a study for MDD (62). However, the development and systematic investigation of a circadian structure therapy for AUD patients has not yet been published and was recently highlighted as a necessity (63). Thus, with DAILY we develop a new treatment approach for AUD patients, partly based on established concepts of chronotherapies for other mental disorders and implement it alongside standard AUD therapies.

We assume that subjects in our study benefit from the reduction of physical conditions that promote and maintain alcohol consumption behavior. We further believe that the strengthening of circadian rhythms has not only positive effects on alcohol craving, but also on often accompanying symptoms of AUD, such as depressive mood. Therefore, we have called this newly proposed intervention for AUD patients DAILY, which stands for **D**epression **A**lcohol **Il**lness Therap**y**.

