## Study Design

### Design

The study is a 6-weeks trial with a controlled, randomized, single-blinded, parallel-group design including patients with a diagnosis of AUD. Patients are randomly assigned to either an intervention group (DAILY) or a sham control group (placebo treatment). As this study represents a pilot randomized trial, which does not primarily focus on proving treatment successes but more on ascertaining the best options for the future main trial, we will include each eligible patient within this year instead of using formal power calculations (64).

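### The final 30-day drinking look-back leaves roughly the first 7–12 days after the first session without a described day-level drinking record

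*Protocol article*

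**What the plan says.** The Abstract of the protocol article states that "the primary outcomes of this study are improvements of regularity, alcohol consumption, and relapse rate in AUD patients". Measured Outcomes names drinking behavior as primary alongside the Routine Variability Score.

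Under Design, "The study is a 6-weeks trial". Counts of drinks and abstinent days "within the past 30 days is assessed by means of the Timeline Followback 30 (TLFB-30"). Table 1 marks this instrument at the first and last sessions, with nothing between sessions.

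Measured Outcomes divides the work between instruments: "Drinking behavior and daily craving will be assessed with questionnaires and the diary, respectively". The list of diary items in the Week 1 section for the intervention group includes craving and does not include drinking.

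Three further statements bear on what falls in the early days. For newly admitted ward patients, enrolment "will take place at the earliest after 5 days of detoxification". "The treatment of AUD patients on the ward is scheduled for 14 days". The background section on the transition from inpatient to outpatient care says that this phase "often represents a stressful and thus susceptible time for alcohol relapses".

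Measured Outcomes also plans weekly Routine Variability Scores, to see whether relapses go with irregularity in the same week.

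**The concern.** A 30-day look-back taken about six weeks after the first session cannot reach the first session. The days it misses are not a run-in. Recruitment places allocation before the first session, and the legend of Figure 1 says that the content discussed on the consent day already differs between groups. The intervention group has its circadian psychoeducation in week 1. Drinking on these days therefore happens after randomisation and belongs to an intention-to-treat comparison of relapse.

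Two things are at stake. A patient who drinks only in the uncovered days and then abstains has no drinks on the final interview and would count as not relapsed on that measure. And the weekly analysis of relapse against irregularity has diary scores for the test-diary week, but no described drinking data for most of it.

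**Working it through.** **Inputs from the protocol article.** Trial length 6 weeks (Design). Look-back 30 days, at first and last session only (Measured Outcomes; Table 1). Psychoeducation a few days after baseline in the same week (Week 1). Plan session one week later (Week 2). Last session 2 + 2 weeks = 28 days after the plan session (Weeks 3–6). Ward stay 14 days, with enrolment from detoxification day 5. Day-clinic stay 2–4 weeks.

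**Stated length reproduced.** By the section headings, 7 + 7 + 28 = 42 days, which is the stated 6 weeks.

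**Uncovered days.** The psychoeducation day is not fixed, so I take it as day 2 to 7 after the first session (assumption).

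- Plan session = psychoeducation day + 7
- Last session = plan session + 28
- Uncovered days = last session − 30

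| Psychoeducation day | Plan session | Last session | Uncovered days | Share of follow-up |
|---|---|---|---|---|
| 2 | 9 | 37 | 7 | 7/37 = 18.9% |
| 3 | 10 | 38 | 8 | 8/38 = 21.1% |
| 5 | 12 | 40 | 10 | 10/40 = 25.0% |
| 7 | 14 | 42 | 12 | 12/42 = 28.6% |

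The legend of Figure 1 describes the test diary as lasting at least a week. Every extra day there adds one uncovered day.

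**Which phase is missed.** The look-back starts 30 − 28 = 2 days before the plan session. None of the 28 plan days is lost. Of the 7 test-diary days, about 7 − 2 = 5 lie outside the look-back, together with the days before psychoeducation.

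**Post-discharge days missed, ward patients.** Discharge on the study clock = 14 − detoxification day at enrolment. Missed post-discharge days = max(0, uncovered days − discharge day).

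| Enrolled on detoxification day | Discharge, study day | Missed if 7 uncovered | Missed if 12 uncovered |
|---|---|---|---|
| 5 | 9 | 0 | 3 |
| 7 | 7 | 0 | 5 |
| 10 | 4 | 3 | 8 |

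**Day-clinic patients enrolled at admission.** Discharge falls on study day 14 to 28, so max(0, 12 − 14) = 0 days are missed.

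**The case against.** The strongest reply is that the look-back covers the whole of the plan phase, which is the core of the intervention, and that the trial is a pilot not mainly aimed at proving efficacy. The first half is correct and limits the point. It does not remove it, because the uncovered days still follow allocation and relapse rate is still listed as primary.

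A second reply is that drinking may be recorded elsewhere. The diary form is a supplementary table that is not shown, and the planned weekly relapse analysis implies that relapse timing is captured somewhere. This stands as a caveat. The text as written gives drinking to the questionnaires and craving to the diary. AUDIT is described only as covering recent weeks, EuropASI has no stated recall period, and neither is described as yielding dated drinking days.

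Some stronger readings are tempting but are not supported:

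- *The early days never enter the primary outcome.* The Routine Variability Score is also primary and can draw on the diary from week 1, and AUDIT may reach part of the period. Only day-level drinking is missing.
- *The trial misses the transition it targets.* The Weeks 3–6 section places many discharges and transfers in that phase, inside the look-back. The loss depends on enrolment day, and some ward patients move to the day clinic or another institution rather than home.
- *About a third of relapses are lost.* With a constant hazard and 30–60% relapse by the last session (both assumed), 32–38% of first drinks fall in the first 12 of 42 days, and about 24–29% in the first 8 of 38. These are first drinks, not misclassified patients: anyone who drinks early and again in the last 30 days is still detected. The hazard may also be lower while patients are on the ward.
- *Uneven baseline look-backs spoil the start-to-end change.* Protected days before the first session do vary between patients, but they affect both randomised arms, so a systematic distortion of the comparison does not follow.
- *The listed tests cannot handle relapse.* Data Analysis gives those tests as examples, and endpoint-specific detail may sit in a document not shown.

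**Conclusion.** The point holds in limited form. By the article's own schedule, about 7–12 days after the first session (19–29% of follow-up) have no described day-level drinking record. They are post-allocation days in the psychoeducation and test-diary phase. For ward patients on the 14-day schedule they can include early post-discharge days: 0–3 with enrolment on detoxification day 5, and 3–8 with enrolment on day 10. The consequence is confined to patients who drink in this period and then abstain through the last 30 days, and to the weekly relapse analysis for most of the test-diary week. How many patients that is cannot be worked out from the document.

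The conclusion assumes that psychoeducation falls on day 2–7, that the sessions keep to the described intervals, and that the unseen diary form has no drinking item. If it has one, the gap is largely closed and the text should say so. This is an inexpensive improvement to a primary measure, not a flaw that undermines the trial.

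**What to change.** At the last session, run the Timeline Followback back to the date of the first session (about 37–42 days) instead of a fixed 30. Derive the primary relapse outcome from that record, as any drinking day since the first session, with its date. Report the last 30 days separately, so that they remain comparable with the baseline 30-day interview. Amend Table 1 and Measured Outcomes to match. If the diary already records drinking, state this and name it as the source for the weekly relapse analysis.

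The cost is a few more interview minutes per patient, recall over 7–12 more days, and a change of wording.
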